### Ethical issues

The study protocol is approved by the Ethics Committee of the Lübeck University (reference number: 16–176). Participants will not receive monetary compensation for their participation. All data will be stored securely and pseudonymized. The data collected via computer administered assessments do not include any patient identifiable information. Personal data and video files are stored and secured on servers protected by the university's information technology services. Published material will not contain any patient identifiable information. Protocol amendments or changes will be communicated to relevant parties.

### Risks and benefits

Both study conditions are active psychological treatments with efficacy demonstrated in previous research and without known iatrogenic effects besides side effects of psychotherapy. Participants in this trial will be monitored intensively so that any worsening or suicidal risk can be identified and dealt with immediately. Participants that become suicidal during the course of their participation in this study will receive enhanced therapeutic assistance or will be referred to an inpatient setting within the University Hospital as appropriate. The psychiatric emergency service of our department is available for patients at any time.

### Curent state of the trial

Recruitment, enrollment and treatment of participants has started.

## Discussion

In this article the study design of the PRO^*^MDD trial is described, which is a controlled randomized trial that compares the clinical effectiveness of BA and MCT in the treatment of MDD. The primary hypothesis is that the two treatments significantly differ in reducing depressive symptoms. To the best of our knowledge, the PRO^*^MDD study is the first RCT comparing the effectiveness of BA and MCT in the treatment of MDD.

BA and MCT have different underlying assumptions regarding the development and maintenance of depressive symptoms and use different approaches and treatment techniques. It is therefore hypothesized that there will be differences regarding the main outcome measure (severity of depressive symptoms) as well as psychosocial functioning, quality of life and other secondary outcome measures (rumination and worrying, avoidance behavior, emotion regulation, comorbidity). The two methods will also be examined regarding their effectiveness in different subgroups of MDD patients (e.g., with and without comorbid anxiety disorders or personality disorders, different subtypes of depressive disorders, with or without presence of early trauma). Thus, comparing the two treatment methods can yield important insights to advance our knowledge on psychotherapy for MDD and generate new hypothesis about process parameters leading to change, differential effects, and predictors.

Among the strengths of the PRO^*^MDD study is the common framework that guarantees equipoise of the two study conditions. Also, both treatment conditions work with written manuals that have been used in previous scientific research trials (37, 38, 40–43). In both conditions, treatment is provided by trained therapists under close supervisions and with high allegiance to the specific method. Well-known and established instruments will be used as outcome measures, which allow comparability with other research trials. All outcome measures are assessed by blind, trained, and independent raters. The repeated measurements allow close monitoring of changes over time. The 2 year follow-up period enables the observation of long-term effects of the two treatment methods. Another strength of the PRO^*^MDD study is its implementation in routine clinical care. As minimal exclusion criteria are applied, generalizability and ecological validity are high.

A limitation of the PRO^*^MDD study is that a two-sided primary hypothesis was used instead of a superiority hypothesis of one therapy method or a non-inferiority hypothesis. The reason for choosing a two-sided hypothesis is based on the fact that there is no prior data that justifies a superiority hypothesis of one method above the other, and that for a non-inferiority trial, the power of this study is not expected to be sufficient. As this is the first study to compare BA and MCT for patients with MDD, it intends to generate pilot data for orientation and hypothesis generation for future research to build upon. The sample size was calculated to detect differential treatment effects of a medium effect size. As both treatment methods are known to be effective, between-group differences may be small and therefore not reach statistical significance. Nevertheless, this study will contribute to building a database of comparisons of treatments for MDD which can be used to identify differences in treatment methods using meta-analytic techniques. A further limitation is that the study does not include a control group such as waitlist-control or treatment as usual. Therefore, non-specific factors such as time cannot be controlled for. We decided against an inactive control group for ethical reasons; as most patients treated in this study setting display complex symptomatology, high comorbidity and chronicity, we will try to minimize the time until they can access treatment. Also, a control group with no treatment or treatment as usual might increase resistance of patients and therapists to participate in the trial and this might endanger the representativeness of the study group and the practicability of patient recruitment. Another issue that needs to be discussed is the different treatment durations recommended for the treatment methods. In most MCT studies, treatment duration is a maximum of 10–12 sessions whereas initial studies of BA included up to 24 sessions (36, 80). To guarantee equipoise of the treatment framework, a maximum of 20–24 individual sessions and 24 group sessions is offered to patients in both treatment conditions. In case of early remission, discontinuation of treatment is possible at mid-treatment (after approximately 10–12 sessions). As previous research has shown that a small number of MCT sessions can already lead to substantial improvement in depressive symptoms, it is hypothesized that MCT will lead to a faster symptom reduction than BA.

The PRO^*^MDD study will be conducted in only one center (Lübeck University). This single-center approach has the advantage that adherence to the research protocol as well as organizational and logistic issues are easier to handle than in a multicenter trial. However, it may have implications regarding the generalizability and external validity. As the PRO^*^MDD study will be conducted in an University Hospital setting which treats patients with complex symptomatology and high comorbidity the study population included in this trial will probably show higher symptom severity, chronicity, and comorbidity compared to the general MDD population in Germany.

In conclusion, the PRO^*^MDD study will further our knowledge on the treatment of MDD as both BA and MCT are promising therapeutic methods for this patient group. By investigating both methods in terms of clinical effectiveness but also regarding process parameters, the PRO^*^MDD study will contribute to the development of the best treatment practice for patients with MDD.

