### Randomization

After completion of the baseline assessment, participants are randomised equally (1:1) to the two groups (MCT or BA). Randomisation is stratified by gender to avoid biases due to unbalanced gender distribution. Randomization will be conducted by using the program BiaS (11.02) (50). The allocation is concealed from participants and researchers. After randomization, participants are informed about the start date of the treatment. In the first treatment session participants will be informed about which condition and therapist they are assigned to.

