### Assessments

Assessments are scheduled at baseline, pre-treatment, mid-treatment (3 months after treatment start) and treatment completion (6 months after start). Follow-up assessments will be conducted at 12, 18, and 30 months after treatment start. Assessments include interviews (conducted by blind and independent research assistants and clinicians trained in the interviews) and self-report measures (administered by a computer). Assessment time points are summarized in Table 2.

**Table 2 T2:** Interviews and questionnaires used at each assessment.

	**Baseline**	**Pre-treatment**	**Mid-treatment**	**Post-treatment**	**Follow-up assessments**		
			**3 months**	**6 months**	**12 months**	**18 months**	**30 months**
HRSD	•	•	•	•	•	•	•
QIDS-C16	•	•	•	•	•	•	•
SKID-I	•				•	•	•
SKID-II	•				•	•	•
Structured assessment depression	•			•	•	•	•
WHODAS 2.0	•		•	•	•	•	•
Demographic questionnaire	•			•	•	•	•
Medication questionnaire	•		•	•	•	•	•
CTQ	•					
PHQ-9	•		•	•	•	•	•
BSI	•		•	•	•	•	•
SF-12	•		•	•	•	•	•
MDD-S	•		•	•	•	•	•
MCQ-30	•		•	•	•	•	•
RSQ-D	•		•	•	•	•	•
BADS	•		•	•	•	•	•
DERS	•		•	•	•	•	•
CDQ			•	•		

*HRSD, Hamilton Rating Scale for Depression; SCID I, Structured Clinical Interview for DSM-IV Axis-I Disorders; SCID-II, Structured Clinical Interview for DSM-IV Axis-II Disorders; CTQ, Childhood Trauma Questionnaire; QIDS-C16, Quick Inventory of Depressive Symptomatology; Clinician Rating; PHQ, Patient Health Questionnaire; WHODAS 2.0, World Health Organization Disability Assessment Schedule 2.0; BSI, Brief Symptom Inventory; SF-12, Short Form-12 Health Survey; MDD-S, Major Depressive Disorder Scale; MCQ-30, Metacognitions Questionnaire; RSQ-D, Response Style Questionnaire; BADS, Behavioral Activation of Depression Scale; DERS, Difficulties in Emotion Regulation Scale; CDQ, Care Dependency Questionnaire*.

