### Outcome measures

#### Primary outcome measure

*Primary outcome measure* is depressive severity assessed by the 24-item version of the Hamilton Rating Scale for Depression (HRSD-24) (47), a semi-structured interview measuring severity of all symptom domains of depression described by the DSM-IV over the last 7 days. The HRSD has shown good psychometric qualities (47, 53). A cutoff of 16 points has been defined as indicating the presence of a moderate depressive episode and a total score of ≥16 points will be handled as inclusion criterion in this study (54). Remission of depression is defined as an HRSD score of ≤ 8, response as a reduction of 50% in the baseline total score of the HRSD (46, 55) and a score of 15 or less, but of more than 8.

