#### Secondary outcome measures

*Secondary outcome measures* are assessed by interview or self-report. They include the following measures.

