### Process parameters

The MDD-S, the BADS and the self-rating version of the QIDS (QIDS-SR16) will be used as process parameters. In the MCT condition, the QIDS-SR16 and the MDD-S will be assessed weekly and the BADS monthly. In the BA condition, the QIDS-SR16 and the BADS will be assessed weekly and the MDD-S monthly.

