### Statistical analyses

Hypothesis will be tested by performing analyis on the whole database including all randomized patients (intention-to-treat analysis). Multiple imputation procedure will be used to replace missing data. We will use linear mixed models (LMM) as they have the advantage of using all available data of each subject. LMM analyses also offer the opportunity to choose an appropriate covariance structure reflecting the potential dependence due to repeated measurements (77). Adjustment for baseline measure will be chosen as this increases statistical power and accounts for regression to the mean (78). All continuous outcomes will be analysed as change from baseline with a random intercept for the participant, time as within-groups factor, study group as well as gender as fixed effect and adjustment for baseline measure. The study hypothesis will be tested on the main effect for group. The estimation of effect size will be based on the imputated dataset and Cohen's d will be calculated for continuous data and numbers needed to treat (NNT) for binary data. The appropriate forms of mixed regression will be chosen for categorical outcome variables, counts and in case of non-normal residuals (poisson, gamma, negative binominal, etc.). To identify predictors or moderators related to treatment outcome, mixed regression methods will be used.

Negative effects will be identified by analyzing and reporting the amount of participants that experienced a clinical significant deterioration [according to Jacobson and Truax (79)].For the time to event analysis, onset of remission will be used as the dependent variable and group assignment as the independent variable. Here, remission will be defined as a score of < 6 on the weekly QIDS-SR16 rating. Patients who do not achieve remission within the 6 months of treatment or dropped out will be censored. No missing data will be substituted for this analysis. The *Kaplan-Meier method* will be used to estimate time to remission (in weeks) and remission rates. The main hypothesis will be tested by comparing the estimated remission rates in both groups using the log-rank test. *Cox proportional hazards regression* will be used to calculate the hazard ratios, to evaluate the influence of covariates for the adjusted analyses and to perform the subgroup analyses.

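### The Discussion says blind raters assess every outcome, but the self-report outcomes and the time-to-remission endpoint come from patients who know their treatment

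*Protocol article*

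**What the plan says.** In the Discussion of the protocol article, the paragraph on strengths contains this sentence, with no exception: "All outcome measures are assessed by blind, trained, and independent raters".

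The Methods describe something narrower:

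- **Assessments:** measurement consists of "interviews (conducted by blind and independent research assistants and clinicians trained in the interviews) and self-report measures (administered by a computer"). The word blind is attached to the interviewers only.
- **Secondary outcome measures:** the section names two modes for these outcomes, interview and self-report.
- **Randomization:** "In the first treatment session participants will be informed about which condition and therapist they are assigned to".
- **Process parameters:** "The MDD-S, the BADS and the self-rating version of the QIDS (QIDS-SR16) will be used as process parameters".
- **Statistical analyses:** for the time-to-event analysis, "remission will be defined as a score of < 6 on the weekly QIDS-SR16 rating".
- **Primary outcome measure:** the HRSD-24 is "a semi-structured interview measuring severity of all symptom domains of depression described by the DSM-IV over the last 7 days".

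**The concern.** Blind outcome assessment is a specific protection against bias, and the Discussion claims it for every outcome. A self-rating has no independent rater. The person who gives the score is the patient, who knows the treatment from the first session on.

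The overstatement matters most for speed of remission. The Introduction motivates the time-to-event analysis by MCT's reputation for bringing about remission quickly, and the Discussion hypothesizes faster symptom reduction with MCT. The Discussion also says that therapists in both arms hold high allegiance to their own method. A directional expectation therefore exists among the investigators, and the comparison that tests it uses an unblinded self-rating collected during therapy. A reader who relies on the Discussion sentence would take that comparison, and the self-reported secondary results, to be protected by blind rating. The limitations given in the Discussion (two-sided hypothesis, no inactive control, different usual treatment lengths, single centre) do not mention unblinded self-report, so nothing there corrects the impression.

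**Working it through.** **1. The plan's own figure.** The one computable design figure is 64 patients per arm, from d = 0.5, two-sided 5% and 80% power. The normal approximation gives n = 2(1.960 + 0.842)² / 0.5² = 62.8, so 63. The two-sample t-test gives 63.77, so 64, with power 0.801 at 64. The figure reproduces, and nothing below changes it.

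**2. The claim set beside the Methods.**

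| Outcome | Mode in the article | Blind rater? |
|---|---|---|
| HRSD-24 (primary) | Semi-structured interview | Yes, by the Assessments section |
| QIDS-C16, SCID-I, SCID-II | Clinician rating or interview | Yes, by the Assessments section |
| Self-report secondary outcomes | Computer-administered | No rater; patient knows the arm |
| Time to remission | Weekly QIDS-SR16, named as a self-rating | No rater; patient knows the arm |

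The last two rows contradict the Discussion sentence. The contradiction needs no count of scales: the Assessments and Secondary outcome measures sections say that some outcomes are self-report, and the Process parameters section calls the QIDS-SR16 a self-rating.

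**3. When the self-reports become unblinded.** Baseline assessment precedes randomization. Table 2 schedules only the HRSD and QIDS-C16 at pre-treatment. In that table every self-report after baseline therefore falls at 3 months or later, when patients know their arm. The weekly QIDS-SR16 ratings are process measures taken during treatment.

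**4. How many scales are involved.** Table 2 has 18 rows. Leaving out the HRSD, the demographic and medication questionnaires, and the CTQ (given once, before treatment) leaves 18 − 4 = 14 instruments:

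- Four are read as interview or clinician rated: QIDS-C16, SCID-I, SCID-II and the structured depression assessment.
- Four carry the word questionnaire in their names: PHQ-9, MCQ-30, RSQ-D and CDQ.
- Five have names that do not settle the mode: BSI, SF-12, MDD-S, BADS and DERS.
- One, the WHODAS 2.0, has no stated mode.

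The self-report share depends on how the unsettled scales are read:

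- Only those named as questionnaires: 4/14 = 29%.
- Adding the five unsettled scales, with the WHODAS as an interview: 9/14 = 64%.
- Adding the WHODAS as well: 10/14 = 71%.

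The middle and upper readings are the natural ones, but they are inferences. The QIDS-SR16 is not in Table 2 and comes on top of each count.

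**5. Whether a blind-rated check exists.** The HRSD is scheduled at 3 months, and the Primary outcome measure section defines remission as a score of 8 or less. The Treatment retention section says that, for patients remitted at 3 months who stop early, the post-treatment assessment takes the place of the mid-treatment one. Their 3-month HRSD therefore carries the post-treatment label. Classifying by time since treatment start instead of by visit label puts them in the 3-month comparison. A 6-month comparison is less clean, because the article does not say how these patients would count then.

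**The case against.** The strongest reply is that this is one loose sentence in a Discussion. The operative Methods text is correct and open: it limits blind raters to interviews, names self-report, and identifies the QIDS-SR16 as self-rated. No procedure, analysis or decision rule depends on the sentence, and self-report is a legitimate choice. All of that stands. The fault lies in the description of the design, and the design itself is not at fault. It is still more than clerical, because the sentence is offered as a strength that bears on what the trial can conclude.

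Several stronger readings are tempting and should be resisted:

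- **The primary result is unprotected.** It is not. The HRSD-24 is an interview done by blind assessors.
- **Most secondary outcomes are proven to be self-report.** This is likely, but the article does not label every scale. Four of the nine presumed self-reports (MDD-S, MCQ-30, RSQ-D, BADS) are classed as method-specific measures, and the shorter list of secondary outcomes in the Introduction includes comorbidity and attrition, which are not self-ratings.
- **The speed result will be biased towards MCT.** The faster-MCT hypothesis is the investigators'. Nothing shows that patients are told of it, and both arms are active treatments in a similar framework.
- **A speed claim should require the blind-rated result to agree in direction.** Such a rule has no error control, and correlated measures will often share a sign by chance. It is out of place in a trial described as a hypothesis-generating pilot.

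It is also fair to say that HRSD remission is already defined, that methods for binary outcomes are planned, and that further sensitivity analyses may sit in an analysis plan that is not shown. The added comparison is therefore a supportive suggestion, and its absence from the article is no defect.

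**Conclusion.** The Discussion sentence is wrong as written and conflicts with five parts of the Methods: Randomization, Assessments, Secondary outcome measures, Process parameters and Statistical analyses. It attributes blind rating to self-report outcomes and, most importantly, to a time-to-remission endpoint that depends wholly on an unblinded self-rating. It should be corrected, because it affects how a speed-of-remission result may be interpreted.

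The scope is limited. The primary analysis and the sample size are untouched. The article does not fix the number of self-report scales, and neither the size nor the direction of any bias can be derived from it. The conclusion rests on the explicit statements about interviews, self-report and disclosure of allocation, and does not depend on the count.

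**What to change.** 1. In the Discussion, restrict the sentence to interview-based outcomes (HRSD-24, QIDS-C16, SCID), and state that self-report outcomes, including QIDS-SR16 remission, are not blinded.
2. Add this to the limitations as a caveat on any conclusion about speed of remission.
3. As a supportive check, report the between-arm comparison of blind-rated HRSD remission (≤ 8) at the 3-month assessment beside the log-rank result. Count early successes by their assessment at that time, although it is labelled post-treatment. Set no formal rule that the two results must agree.

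The cost is a less favourable account of the trial and one extra analysis of data already scheduled. That analysis is coarse: it measures remission at a fixed visit, which is a different quantity from time to remission, so it can support or qualify the log-rank result but cannot replace it.

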## Ethics statement

The study was approved by the ethics committee of Lübeck University. Written informed consent will be obtained from all participants prior to inclusion in the study.

## Data availability statement

Individual patient data will be shared with researchers who provide a methodologically sound proposal. Proposals can be submitted up to 36 months following publication of the main results.

## Abbreviations

PRO^*^MDD: Programs for Major Depressive Disorder
MDD: Major Depressive Disorder
BA: Behavioral Activation
MCT: Metacognitive Therapy
WHO: World Health Organization
RCT: Randomized Controlled Trial
DSM-5, Diagnostic and Statistical Manual of Mental Disorders: 5th Edition
DSM-IV, Diagnostic and Statistical Manual of Mental Disorders: 4th Edition
CBT: Cognitive behavior therapy
CAS: Cognitive-Attentional-Syndrome
DM: Detached Mindfulness
HRSD: Hamilton Rating Scale for Depression
SCID I: Structured Clinical Interview for DSM-IV Axis-I Disorders
SCID-II: Structured Clinical Interview for DSM-IV Axis-II Disorders
QIDS-C16, Quick Inventory of Depressive Symptoms: clinician-rating
QIDS-SR16, Quick Inventory of Depressive Symptoms: self-rating
BSI: Brief Symptom Inventory
WHODAS 2.0: World Health Organization Disability Assessment Schedule 2.0
SF-12: Short Form-12 Health Survey
MDD-S: Major Depressive Disorder Scale
MCQ-30: Metacognitions Questionnaire
RSQ-D: Response Style Questionnaire
BADS: Behavioral Activation of Depression Scale
DERS: Difficulties in Emotion Regulation Scale
CTQ: Childhood Trauma Questionnaire
NNT: number needed to treat.
